# Education to keep the abdomen relaxed versus contracted during pilates in patients with chronic low back pain: study protocol for a randomised controlled trial

**DOI:** 10.1186/s12891-023-06160-z

**Published:** 2023-01-20

**Keywords:** Exercise movement techniques, Chronic pain, Low back pain

## Abstract

**Background:**

Low back pain is a very common symptom frequently characterized as a biopsychosocial problem. This study aims to investigate the effectiveness of education to keep the abdomen relaxed versus contracted during Pilates exercises in patients with primary chronic low back pain.

**Methods:**

Two-group randomised controlled trial with allocation of parallel groups and intention-to-treat-analysis. This study will be conducted in Lavras, MG, Brazil. A total of 152 participants will be randomised into two groups that will be treated with Pilates exercises for 12 weeks (twice a week for 60 minutes). Recruitment began in May 2022. The control group will receive guidance on the specific activation of the center of strength (the powerhouse), while the experimental group will receive guidance to perform the exercises in a relaxed and smooth way. Primary outcomes will be pain intensity (Numeric Pain Rating Scale) and disability (Rolland-Morris Questionnaire) 12 weeks post randomisation. Secondary outcomes will be global improvement (Perception of Global Effect Scale) and specific functionality (Patient-specific Functional Scale). The outcomes will be analyzed using repeated-measure linear mixed models. The assessors were not considered blinded because the participants were not blinded, and outcomes were self-reported.

**Discussion:**

The findings of this study will help in clinical decision-making concerning the need to demand abdominal contraction during the exercises, understanding if it’s a fundamental component for the effectiveness of the Pilates method for this population.

**Trial registration:**

This trial was prospectively registered in the Clinical Trials (NCT05336500) in April 2022.

**Supplementary Information:**

The online version contains supplementary material available at 10.1186/s12891-023-06160-z.

## Background

Low back pain is a very common symptom and the causes of its onset and its specific sources of nociception are rarely identified [1]. It is characterized often as a biopsychosocial problem associated with the experience of pain and disability, covering a range of factors that include biophysical, psychological, and social dimensions. Low back pain impairs social function and participation, in addition to personal financial prosperity, since additional costs are associated with chronic conditions [2]. There is a need to reduce unnecessary and even harmful health care, and most importantly, to promote an active lifestyle and adopting healthier habits [3].

The Pilates method is an important component in the treatment of primary chronic low back pain [4–6]. Hayden et al. (2021) conducted a systematic review evaluating the impact of exercise treatment on pain and functional limitations in adults with chronic nonspecific low back pain. They emphasized Pilates as one of several effective methods when compared to no treatment, placebo or usual care [7]. In patients with chronic low back pain, the beneficial effects of Pilates have been observed within 12 weeks, mainly in reducing pain and improving function. Sessions are recommended to last around 60 minutes, with a frequency of two and three times a week, supervised by certified physical therapists [8]. It is important that the exercises include isometric strengthening, global stretching, breathing, and proper positioning of the spine, promoting greater body awareness [9].

Pilates is an effective exercise method for rehabilitation of musculoskeletal disorders, as its principles are based on the activation of local muscles [10]. Specifically in chronic low back pain, clinical trials conducted using exercise protocols based on the principles of the method demonstrate its effectiveness [11–15]. In this sense, motor control of the lumbar spine and maintenance of adequate body posture during the execution of each Pilates exercise is relevant [16].

The real importance of activating muscles such as transversus abdominis and multifidus in chronic musculoskeletal pain conditions is still debatable [17, 18]. Contrary to the fact that muscular components of the trunk influence body stabilization, voluntary activation of the abdominal bracing can limit movements and increase mechanical stress, resulting in greater energy consumption [18, 19]. In patients with chronic low back pain, the transversus abdominis muscle appears to show no delay during activation [17]. Furthermore, multifidus activity can be modified independently of abdominal bracing activation [18]. Individuals with chronic low back pain exhibit higher global trunk muscle activity (multifidus, erector spinae, external oblique, and rectus abdominus )[20]. Interestingly, symptomatic individuals have increased erector spinae muscle activity (longissimus, iliocostalis, and multifidus) during the performance of functional tasks, contradicting the idea of stimulating the muscle activity [21]. Interestingly, patients with chronic low back pain have increased erector spinae muscle activity (longissimus, iliocostalis, and multifidus) during the performance of functional tasks, contradicting the idea of stimulating the muscle activity on these patients [21].

Consequently, a question arises about the need to encourage abdominal muscles contraction instead of relaxation during the performance of Pilates method exercises for the treatment of chronic low back pain. Therefore, the primary objective of this study is to investigate the effectiveness of education to keep the abdomen relaxed compared to contracted during Pilates exercises in reducing pain and disability in patients with primary chronic low back pain 12 weeks after randomisation.

## Methods and design

### Design and setting

The protocol was written according to the SPIRIT statement (Fig. 1), increasing its transparency and completeness [22]. The findings will be reported following the CONSORT statement [23] and the TIDieR checklist [24]. This study is a research protocol for a two-group randomised controlled trial with parallel-group allocation and intention-to-treat analysis (Fig. 2). The study will be conducted in Lavras, MG (Brazil).

**Fig. 1 Fig1:**
[figure not shown]
Content for the schedule of enrolment, interventions, and assessments (SPIRIT 2013)

**Fig. 2 Fig2:**
[figure not shown]
Study flowchart

### Recruitment and participants

We will screen patients of both sexes with primary chronic low back pain with symptoms for at least 12 weeks and who have not had an episode of worsening pain in the last 6 weeks (Table 1). Initially, participants will be evaluated by a physical therapist who is blinded to the allocation of intervention groups, confirming their eligibility according to the inclusion and exclusion criteria (Table 2). This screening will involve the survey of a brief history and the application of a questionnaire related to disability, as it characterizes one of the inclusion criteria. Eligible patients will be informed about the objectives and procedures of the study. They will be informed that there are two active interventions, but it is not yet known which one is superior. Eligible patients that agree to participate in the study will sign a print informed consent form before enrollment. The study started in May 2022, and the recruitment rate is 10 patients per month on average.

**Table 1 Tab1:** Execution schedule – recruitment, intervention, and reassessment (SPIRIT schedule of enrollment, interventions, and assessments)

	Recruitment	Baseline	Intervention period	Re-evaluation
			12 weeks	12 weeks after intervention
**Before randomisation**				
Eligibility Criteria	x			
Selection	x			
Informed consent	x			
**Primary outcomes**				
Pain intensity		x		x
Disability level		x		x
**Secondary outcomes**				
Perception of global improvement		x		x
pecific functionality		x		x
**Characteristics of participants**				
Demographic data		x		
Duration of low back pain		x		
Risk of chronicity		x		
Map of pain regions		x		
Life stress events		x		
MRI performed		x		
Family history of low back pain		x		
Pilates practice history		x		
Pilates exercises associated with relaxed abdomen			x	
Pilates exercises associated with contracted abdomen			x

**Table 2 Tab2:** Inclusion and exclusion criteria for research participants

Inclusion criteria	Exclusion criteria
Aged from 18 years old; Low back pain for more than 3 months; Disability level ≥ 4 points on the Roland-Morris Disability Questionnaire (RMDQ); Ability to move independently with or without assistance; Ability to understand Portuguese enough to be able to fill in the questionnaires.	The main area of pain other than the lumbar spine (eg, nerve root compression or herniated disc with radicular pain, lateral or central stenosis); Surgery performed on the lumbar spine; Surgery performed on the lower limbs, or abdominal region less than 6 months ago; Performing an invasive procedure for pain relief (eg, epidural injection, rhizotomy) in the last 3 months; Diagnosis of inflammatory rheumatologic diseases, progressive neurological disease, or viral diseases as the primary cause of pain; Scoliosis as the primary cause of pain; Unstable heart conditions; Presence of red flags such as malignancy/cancer, acute trauma (less than 6 months), infection, spinal cord/cauda equina compression.

### Treatment allocation and randomisation

Initially, a random sequence in blocks will be generated through a computer program by a researcher not involved in data collection. The random codes for treatment will be placed in opaque, sealed envelopes and sequentially numbered, thus assuring the secret allocation of individuals to the study groups. After the initial assessment, inclusion in the study, and baseline data collection, a researcher will open the envelopes and refer the participant to the physical therapist responsible for the respective group of allocation. The patient will start treatment in the same week, with groups of up to 6 patients for each treatment.

In the KAC group (control), patients will receive instructions about breathing and its performance along with muscle action. Patients will receive verbal instructions about the performance of each exercise. During execution, postures will be corrected as needed. All patients in the KAC group will be instructed about the performance of exercises based on specific activation of the musculature (transversus abdominis, diaphragm, obliques, multifidus, and pelvic floor). This characterizes the contraction of the center of strength (core or powerhouse), conceptualized by stabilization depth and activation of abdominal bracing. During the execution of the exercises, the patients will receive stimuli through verbal commands, which will be continuously reinforced, so that the contraction of the muscles is performed throughout the protocol. In the KAR group (experimental), patients will be instructed to perform the exercises in a relaxed and smooth way, keeping only breathing and concentration during their execution. Also, at no time will the participants be instructed to perform abdominal muscle contraction or activation of the center of strength.

The assessment of treatment fidelity will be performed by in vivo observations as well as video recording during the pilot study and along the trial. Therefore, both groups will be monitored, ensuring adequate adherence to the treatment that will be performed as planned.

### Characteristics of participants

Baseline characteristics will include sociodemographic information, symptoms duration, number of pain areas, family history of low back pain, magnetic resonance imaging (MRI) performed, chronicity risk (Örebro Musculoskeletal Pain Questionnaire [OMPQ]), history of Pilates method practice, and life stress events (Table 3). Baseline characteristics (e.g. history of Pilates method practice) may be analyzed as potential predictors or moderators of outcomes.

**Table 3 Tab3:** Characteristics of participants

1) Sociodemographic data, including age and sex, will be obtained; 2) Duration of low back pain (in months) will be obtained through the question: “How long have you had low back pain?”; 3) Risk of chronicity, obtained through the 10 items of the short version of the Örebro Musculoskeletal Pain Questionnaire (OMPQ)[30]; 4) Map of pain regions, where the participant will mark the numbers that correspond to the pain site; 5) Life stress events assessed through closed questions, with dichotomous answers (yes and no), covering the following aspects: serious illness that resulted in withdrawal from usual activities; hospital admission due to illness or accident; death of a close relative; severe financial problems; forced change of housing; separation/divorce; Physical aggression; and assault/robbery; 6) MRI performed, where the following question will be asked: “Have you ever performed a magnetic resonance imaging (MRI) for the lumbar spine?” Answer options: yes or no; 7) Family history of low back pain, where the following question will be asked: “Do you have anyone in the family who suffers from low back pain?” Answer options: yes or no; 8) History of Pilates method practice, where the following question will be asked: “Have you ever practiced Pilates?” Answer options: yes or no.	

### Outcome measures

Co-primary outcomes will be pain intensity (Numerical Pain Scale) and disability (Roland-Morris Disability Questionnaire) related to primary chronic low back pain assessed 12 weeks after randomisation, obtained through self-report. Secondary outcomes will be global improvement (Perception of Global Effect Scale) and specific functionality (Patient-specific Functional Scale) assessed 12 weeks after randomisation (Table 4).

**Table 4 Tab4:** Primary and secondary outcomes

Outcome	Measurement
1st) Pain intensity	The Brazilian version of the 11-point Numerical Pain Scale (NPS) [22, 31], which varies between 0 and 10 points, where 0 is “no pain” and 10 is “the worst pain imaginable” where individuals should report pain intensity based on the last 7 days;
2nd) Disability	The Brazilian version of the Roland-Morris Disability Questionnaire (RMDQ) [32], which has 24 statements involving activities and pain situations, to which the patient is instructed to answer “yes” only to those described in the assessment day, and each answer corresponds to one point;
3rd) Perception of global improvement	Perception of Global Effect Scale (PGES), 11 points ranging from −5 (“much worse”), 0 (“no change”) to + 5 (completely recovered) [22]. For all measures of perceived global effect participants will be asked: “Compared to the start of your first episode, how do you describe your low back pain in the past few days?”. A highly positive score indicates greater recovery, while a negative score indicates worsening of symptoms;
4th) Specific functionality	Patient-specific functional scale (PSFS) [22], which consists of an interview in which the patient chooses three important activities whose execution is difficult or impossible due to low back pain. For each activity, a score of difficulty ranges from 0 (unable to perform) to 10 (able to perform at the same level as before the problem).

### Blinding

It was not possible to blind the participants and the treating clinicians. The assessors were not considered blinded because the participants were not blinded, and outcomes were self-reported. However, to guarantee that the treatment expectation was evenly balanced between the groups and decrease measurement bias, the participants will not know the study hypothesis, and the assessors will not know the participant’s intervention group. The statistician will be blinded to the group allocation.

### Statistical analysis

The analysis of the data obtained during the research will be carried out by a statistical professional who will have access to the coded data and were based on intention-to-treat principles. Missing data will be assumed to be missing completely at random. Multiple imputation will be used to account for these missing data [33]. Missing values in outcome variables will be estimated using multiple imputation by chained equations after 50 replicated imputed data sets. Variables included in the multiple imputation process will include (1) group factor, (2) time factor, and (3) the respective outcome variable. Descriptive statistics will be used to present the characteristics of participants in the two treatment groups. Two-sided *P* values of less than 0.05 will be considered to indicate statistical evidence of significance. The outcomes pain intensity and disability will be analyzed using repeated-measure linear mixed models (participants and time as random factors) that included all the scores that will be reported after randomisation with the baseline scores and treatment clusters as covariates. Adjusted mean differences will be tested at 12 weeks after randomisation. Multiple comparisons will be performed using the Tukey test with *P* values adjusted using the Holm procedure. The baseline variables will be evaluated as predictors and moderators of treatment effects including terms and interaction models. Effect sizes for primary and secondary outcomes will be calculated as Cohen’s d from estimated marginal means and standard error estimates from the primary adjusted analysis. Effect sizes will be interpreted according to Cohen’s criteria (small ≤0.2; moderate = 0.5; large ≥0.8) [34]. All analyses will be performed using the RStudio version 0.99.486.

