### Sample size estimation

The sample size required for this study will be 152 (76 per group) to detect a mean difference of 4.0 points for disability measured by RMDQ and 1.0 for pain intensity measured by NPRS between the two intervention arms, assuming a standard deviation of 4.9 for disability and 2.0 for pain, with an alpha of 5%, power of 80% and a possible loss to follow-up of 15 % [35–37].

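### Missing outcomes are assumed missing completely at random and imputed from arm, time and the same outcome only; this can bias the primary difference if dropout depends on an omitted predictor differently in the two arms

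*Protocol article*

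**What the plan says.** The Statistical analysis section fixes both the assumption and the method.

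- Assumption: "Missing data will be assumed to be missing completely at random".
- Method: "Missing values in outcome variables will be estimated using multiple imputation by chained equations after 50 replicated imputed data sets".
- Imputation model: "Variables included in the multiple imputation process will include (1) group factor, (2) time factor, and (3) the respective outcome variable".

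The same section fits mixed models for pain and disability "with the baseline scores and treatment clusters as covariates". It also says: "The baseline variables will be evaluated as predictors and moderators of treatment effects including terms and interaction models".

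The Characteristics of participants section lists what is collected at entry: "Baseline characteristics will include sociodemographic information, symptoms duration, number of pain areas, family history of low back pain, magnetic resonance imaging (MRI) performed, chronicity risk" (by the OMPQ short form), then previous Pilates practice and life stress events. None of these is in the imputation list. Neither are the other co-primary outcome and the treatment cluster.

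The Sample size estimation section plans "with an alpha of 5%, power of 80% and a possible loss to follow-up of 15" per cent. Table 1 shows one reassessment after baseline. The Blinding section says that participants and treating clinicians are not blinded and that outcomes are self-reported.

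**The concern.** Missing completely at random means that dropout is unrelated to anything, observed or not. That is hard to defend here. Patients attend 24 supervised sessions (twice a week for 12 weeks), know which instruction they receive, and rate their own pain and disability.

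The choices also do not fit together. If the assumption held, the complete cases would already be unbiased, and imputation could help only through variables beyond those in the analysis model. The list contains none. It is in fact smaller than the primary analysis model, because treatment cluster is left out. The baseline characteristics are named as possible predictors and moderators of outcome, yet they are not used where they would make a missing-at-random assumption more credible.

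At stake is the comparison of the two instructions on the co-primary outcomes. If patients at high risk of chronicity leave one arm more readily than the other, that arm looks better than it is, and the listed imputation cannot correct for it.

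**Working it through.** **1. The plan's own sample size.** Inputs from the Sample size estimation section: pain difference 1.0, SD 2.0, alpha 5% (two-sided, from the Statistical analysis section), power 80%, loss 15%.

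- Normal approximation: n = 2 × (1.960 + 0.842)² × (2.0/1.0)² = 62.8, so 63 per arm. The t-based calculation gives 64.
- 64/0.85 = 75.3, so 76 per arm and 152 in total. The stated figure reproduces, and pain drives it (disability needs about 25 per arm before loss).
- Expected loss: 0.15 × 152 = 22.8, about 23 patients. Observed: 0.85 × 152 = 129.2, about 65 per arm.

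**2. What the listed imputation can do.** There is one follow-up. Arm, time and the same outcome can carry the baseline score of that outcome. The analysis model already conditions on arm and baseline score. Imputing from these and then adjusting for them therefore leads, in large samples, to the baseline-adjusted complete-case result.

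**3. When the difference is biased.** Large-sample simulation: 1,000,000 patients per scenario, true difference 0, pain SD 2.0, 15% overall loss. Assumptions that are not in the document: standardised coefficients of 0.4 for baseline pain and 0.4 for a further predictor X on 12-week pain, with a correlation of 0.3 between them. Odds ratios (OR) for dropout are per SD.

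| Dropout depends on | Bias, listed imputation | Bias, X added |
|---|---|---|
| Nothing | 0.00 | 0.00 |
| Baseline pain, same in both arms | -0.01 | -0.01 |
| Baseline pain, opposite by arm | 0.00 | 0.00 |
| X, same in both arms (OR 2) | 0.00 | 0.00 |
| X (OR 2), with 11% vs 19% loss by arm | -0.03 | 0.01 |
| X in one arm only (OR 2 to 3) | -0.07 to -0.12 | 0.00 |
| X in opposite directions by arm (OR 2 to 3) | -0.15 to -0.21 | about 0.00 |
| The unseen outcome, one arm only (OR 2) | -0.15 | -0.12 |

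Bias needs two things together: dependence on an omitted predictor or on the unseen outcome, and a difference between arms. Adding the predictor removes the first kind of bias but hardly touches the second.

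**4. An extreme case.** Suppose one arm loses exactly its worst-risk 15% on OMPQ and the other loses 15% at random. Mean OMPQ among those remaining in the first arm shifts by φ(1.036)/0.85 = 0.274 SD. Let r be the correlation of OMPQ with 12-week pain, ρ that of baseline with 12-week pain, and 0.5 that of OMPQ with baseline pain (all assumed).

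- Without baseline adjustment: 0.274 × r × 2.0 = 0.16, 0.22, 0.27 for r = 0.3, 0.4, 0.5.
- With the planned baseline adjustment, approximately 0.274 × 2.0 × (r - 0.5ρ):
  - ρ = 0.5: 0.548 × (r - 0.25) = 0.03, 0.08, 0.14.
  - ρ = 0.3: 0.548 × (r - 0.15) = 0.08, 0.14, 0.19.

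The formula ignores the slight flattening of the slope caused by the truncation. Simulating the same case gives 0.02, 0.09, 0.14 and 0.09, 0.15, 0.20. So even this case stays at about 0.02 to 0.20 points.

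**5. Scale.** With about 65 observed per arm, the standard error of the pain difference is 2.0 × √(2/65) = 0.35 unadjusted, or 0.35 × √(1 - 0.5²) = 0.30 if baseline and follow-up correlate 0.5.

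**The case against.** The strongest defence is that the label does not change the computation. Chained-equation imputation from arm, time and the outcome's own history is valid if data are missing at random given arm and baseline score. The arms share exercises and schedule and differ only in instruction, participants are not told the hypothesis, and no dropout by arm is reported. All of this stands, and it limits the point to a conditional risk.

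A reader might infer that prognosis-related dropout as such biases the primary result. It does not: dropout driven by baseline severity, or acting alike in both arms, leaves the difference at about zero. A reader might also take 0.16 to 0.27 points, or 16 to 27% of the target, as the bias of the planned analysis. That is the unadjusted difference in the extreme case, and the plan adjusts for baseline.

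Three further limits stand.

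- Omitting the other 12-week outcomes matters little, because one reassessment collects them all and a lost patient normally lacks all of them.
- The mismatch with the moderator models (interactions absent from the imputation model are pulled towards zero) touches only the roughly 15% of imputed values in secondary analyses.
- The absence of a sensitivity analysis from a condensed article is not itself an error, since it may be set out in an analysis plan that is not shown.

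What the defence does not answer is that the article states an implausible assumption and lists an imputation model that ignores useful variables already collected.

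**Conclusion.** The point holds as a badly fixed choice, not as a demonstrated bias. The assumption is implausible for this design, and the listed imputation does almost nothing that the baseline-adjusted model does not already do.

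If dropout depends on a collected but omitted predictor differently by arm, the bias in pain is about 0.02 to 0.2 points, that is 2 to 20% of the 1.0-point target, and about 0 once the predictor is imputed on. This is smaller than the standard error of about 0.30 to 0.35, but it is systematic and cheap to avoid.

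The sizes rest on assumed correlations and dropout patterns. They also rest on the favourable reading that the imputation list carries the baseline score of the outcome. The document supplies neither correlations nor dropout by arm. The point should be corrected before outcome data are analysed; it does not threaten the design.

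**What to change.** 1. Replace the stated assumption with missing at random given arm, baseline scores and named auxiliary variables.
2. Add a short list of collected predictors to the imputation model: baseline values of both primary outcomes, OMPQ, symptom duration, number of pain areas and previous Pilates practice. Include the arm interaction for any moderator that is analysed.
3. Handle treatment cluster as a random effect, or in another parsimonious way that agrees with the analysis model. Fixed class terms are not advisable. With classes of at most six, 76 patients make at least 13 classes per arm, so 12 extra terms on about 65 observed patients if imputation were run by arm.
4. Preferably add one delta-adjusted sensitivity analysis that worsens imputed 12-week scores in one arm, over a range up to the plan's own target differences (1.0 for pain, 4.0 for RMDQ). Richer imputation does not cure outcome-dependent dropout.

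The cost is a little more analysis work. All variables are already collected, and the sample size stays at 152.

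### Exercise classes belong to one arm only, yet the model lists undefined treatment clusters as covariates rather than as a random effect, and the 80% power makes no allowance for clustering

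*Protocol article*

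**What the plan says.** Randomisation is by individual. Under Treatment allocation and randomisation, a researcher opens the envelope and will "refer the participant to the physical therapist responsible for the respective group of allocation"; treatment then starts in the same week, "with groups of up to 6 patients for each treatment". The Intervention section says that two physiotherapists were trained to deliver the protocol and that sessions take place in separate environments without contact.

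Under Statistical analysis, pain and disability are analysed with linear mixed models. The random factors are given in parentheses as participants and time. The model is fitted "with the baseline scores and treatment clusters as covariates". Adjusted mean differences are tested at 12 weeks, and effect sizes come from estimated marginal means. The term *treatment clusters* is not explained anywhere.

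The Sample size estimation section states: "The sample size required for this study will be 152 (76 per group"). The targets there are 1.0 point for pain (SD 2.0) and 4.0 points for disability (SD 4.9). The calculation is made "with an alpha of 5%, power of 80% and a possible loss to follow-up of 15"%. No ICC, class size or design effect is given.

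**The concern.** No class contains patients from both arms, so class is nested in arm. Between-class variation (group dynamics, time slot, the way a session is run) is then part of the error of the arm comparison. The usual way to carry it is a random class effect. The protocol's list of random factors does not include one and places the clusters beside the baseline scores.

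A nested factor entered as a fixed categorical covariate takes over the arm column. If class is left out, the standard error is too small when outcomes within a class are correlated. Either way the quantity affected is the primary result, the adjusted mean difference at 12 weeks on both co-primary outcomes. The sample size section has the matching gap: the analysis acknowledges clusters and the power calculation does not.

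**Working it through.** **Inputs from the protocol.** Pain: difference 1.0, SD 2.0. Disability: difference 4.0, SD 4.9. Two-sided alpha 0.05, power 80%, loss 15%, 76 per arm, classes of at most 6.

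**Assumptions, not in the protocol.** ICC 0.01, 0.05 and 0.10; correlation r = 0.5 between baseline and 12-week score; closed classes, 13 per arm (76/6 = 12.7, rounded up), 26 in all; completers per class m = 6 × 0.85 = 5.1.

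**1. Reproducing 152.** For pain, 1.0/2.0 = 0.5 SD. A two-sample t-test needs 64 per arm for 80% power; 64/0.85 = 75.3, rounded up to 76, total 152. Disability needs only 25 per arm (30 after loss), so pain drives the number. The figure is reached with no design effect.

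**2. Fixed class covariates.** Intercept, arm, baseline and 25 class indicators make 28 columns. The matrix has rank 27, and still 27 with arm removed, so the arm coefficient is not identified separately from class.
- If software drops a class to proceed, the arm coefficient becomes a contrast of two reference classes, with SE 2.0 × √(2/5.1) = 1.25. In one simulated data set (true difference −1.0, ICC 0.05) it was −0.09, −1.36, −1.79 or −2.83 depending only on which classes were the references.
- The difference between the averages of the 13 class means in each arm is estimable, with SE 2.0 × √(2/64.6) = 0.35. That SE contains no between-class variance.
- With class as a random effect, the same data gave −0.90 (SE 0.32).

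**3. Other readings of the term.** If the clusters are therapists, with one per arm, the covariate equals arm. If they are the two arms, nothing is aliased, but class is not modelled.

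**4. Type I error when class is ignored.** Design effect DE = 1 + (m − 1) × ICC = 1 + 4.1 × ICC. True error = 2 × [1 − Φ(1.96/√DE)].

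| ICC | DE | Type I error |
|---|---|---|
| 0.01 | 1.041 | 5.5% |
| 0.05 | 1.205 | 7.4% |
| 0.10 | 1.410 | 9.9% |

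**5. Power at 152.** Completers per arm: 76 × 0.85 = 64.6. With independent patients, pain power is 80.5%. With clustering, SE = 2.0 × √(2 × F/64.6), and power comes from a noncentral t with 26 − 2 = 24 df. Without baseline adjustment F = DE. With adjustment acting on individual variance only, F = m × ICC + (1 − ICC)(1 − r²).

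| ICC | F, unadjusted | Pain power | F, adjusted | Pain power |
|---|---|---|---|---|
| 0.01 | 1.041 | 76% | 0.794 | 86% |
| 0.05 | 1.205 | 70% | 0.968 | 79% |
| 0.10 | 1.410 | 63% | 1.185 | 71% |

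For disability the unadjusted power on the same basis is 99%, 98% and 96%.

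**The case against.** The strongest reply is that the term is undefined in a condensed article, and that *covariate* may be loose wording for a random effect. That cannot be ruled out, but it sits badly with a sentence that lists its random factors and leaves clusters off the list.

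A reader might infer that the treatment effect cannot be estimated at all. The protocol does not support that. It reports adjusted mean differences and estimated marginal means, and an arm difference averaged over class means is estimable even with fixed classes. The SE of 1.25 belongs only to a default coefficient read uncritically. What remains is that the averaged contrast has to be requested deliberately and that its SE is still incomplete.

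The count of 26 closed classes can also be questioned. The protocol reports about 10 recruits a month, roughly 5 per arm, who start in the week of allocation. Over 12 weeks (about 2.8 months) that is about 14 concurrent patients per arm, or three classes of up to six. Patients may well join running classes, so the number and size of clusters could differ in either direction. This objection stands, and it makes the figures illustrative.

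Finally, the power loss depends on an ICC that the protocol does not give, affects pain only, and can be offset by baseline adjustment. A reader might infer that 152 is too few. The protocol does not establish that: with r = 0.5 and ICC 0.01, pain power is above 80%.

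**Conclusion.** The point holds as a fault in the stated model and in the stated basis of the power. Classes are arm-specific, the cluster term is undefined, and none of its literal readings (classes as fixed covariates, therapists, arms) gives a standard error that carries between-class variance. The aliasing of the arm coefficient under fixed classes is algebra and needs no ICC. So is the finding that 152 contains no allowance for clustering.

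The size of the consequence does rest on assumptions. Over ICC 0.01 to 0.10, with about 5 completers per class, type I error is 5.5% to 9.9% if class is ignored. Pain power is 76% down to 63% unadjusted, or 86% down to 71% with r = 0.5. Disability is little affected. Separately, if each arm has a single therapist, as the protocol suggests, no model can separate therapist from treatment.

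**What to change.** In Statistical analysis:
- define *treatment clusters* as the exercise class actually attended;
- remove it from the fixed covariates and fit it as a random effect within arm, with small-sample degrees of freedom such as Kenward-Roger;
- if patients join running classes, use a membership structure that fits rolling entry.

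In Sample size estimation, keep 152, say that it assumes independent patients, and restate the pain power over a range of ICC. State the baseline correlation used, and apply it to individual variance only.

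State as a limitation that therapist and treatment cannot be separated if each arm has one therapist.

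The cost is wording, a restated power figure, and class membership recorded in the analysis file. No extra patients are needed. The downside is that the stated pain power may look less favourable. The model should be settled before the blinded statistician receives the data, so that a rank-deficient fit is not resolved ad hoc.
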